##### Phase 1.4: Improve (Part 1)

In the final phase of stage 1, information collected in the measure and analyze phases will be used to generate solutions to optimize clinical data quality across services. Solutions will address identified process-related issues (eg, deprioritization of documentation tasks and workforce roles and responsibilities) and system-related issues (ie, system design, performance, and usability).

Program-specific *data requirements* and *priorities* will be established to meet funding and regulatory requirements, best practice clinical guidelines, and the specific workflows of each service. In addition, data specifications will be developed to enable efficient and accurate information capture to enable high-quality primary (eg, care delivery) and secondary (eg, reporting, research, and evaluation) uses of data. A solutions selection matrix [43] will be used to propose and rank solutions according to perceived cost benefits and to prioritize recommendations for implementation based on the most urgent needs of the organization.

#### Stage 2: Optimization

##### Phase 2.1: Improve (Part 2)

Stage 2 will use Agile methodology to test and implement changes to clinical documentation processes and clinical information systems over a 12-month period.

Program-specific data optimization will be conducted to meet the specific workflows and funding, regulatory, and clinical requirements of each service. *Data requirements* and *priorities* established in stage 1 will determine the order of the Agile sprints (ie, incremental cycles of changes). At the end of each sprint, data quality will be evaluated by calculating DPU, DPO, DPMO, and the Sigma level statistics as mentioned in the *Phase 1.2: Measure* section. User acceptance, experience, and satisfaction will be evaluated through user surveys, and user feedback from each sprint will be directly incorporated into the next Agile sprint. This iterative optimization method ensures a flexible approach that incorporates both user feedback and statistical measurement.

##### Phase 2.2: Control

At the end of stage 2, governance policies and procedures and a control plan will be developed to allow the process owner to routinely monitor and evaluate the quality of clinical data across the service after implementation.

The control phase is the final phase and a critical part of the LSS DMAIC framework, which ensures that a new or improved process continues to work successfully after its implementation as a regular business process. A *Clinical Data Quality Audit Tool* will be designed to allow the routine evaluation of data quality across services as part of ongoing business practice. Internal policy and procedure documents will be developed, and training will be provided to the relevant departments.

#### Stage 3: Evaluation

The final stage of the study will evaluate changes in the primary and secondary outcomes in the 12 months following the full optimization (Table 5). Outcomes will be measured at T_0_ and at 1, 3, 6, 9, and 12 months after full optimization. Previous studies in Australian RACFs have shown that the time spent on documentation tasks generally increases in the period after the implementation of new or changed systems as users learn the new technology and adjust their workflows [11,12]. Therefore, long-term evaluation is critical for reliably quantifying changes in outcomes and their impact on organizational processes.

**Table 5 table5:** Primary and secondary outcomes and data collection plan.

Outcomes and data source or method					Time point																
					Baseline (T_0_)		Sprints 1 to n						Follow-up								
							T_1_		T_2_		T_n_		T_1 month_		T_3 months_		T_6 months_		T_9 months_		T_12 months_
**Primary outcome**																					
	**Data quality**																				
		**DPU^a^**																			
			EHR^b^ audit	✓		✓		✓		✓		✓		✓		✓		✓		✓	
		**DPO^c^**																			
			EHR audit	✓		✓		✓		✓		✓		✓		✓		✓		✓	
		**DPMO^d^**																			
			EHR audit	✓		✓		✓		✓		✓		✓		✓		✓		✓	
		**Sigma level**																			
			EHR audit	✓		✓		✓		✓		✓		✓		✓		✓		✓	
**Secondary outcomes**																					
	**Care delivery**																				
		**Direct care time**																			
			Self-report survey	✓								✓		✓		✓		✓		✓	
		**Documentation time**																			
			Self-report survey	✓								✓		✓		✓		✓		✓	
		**Other activities**																			
			Self-report survey	✓								✓		✓		✓		✓		✓	
	**Clinical outcomes**																				
		**Pressure injury^e^**																			
			EHR audit	✓								✓		✓		✓		✓		✓	
		**Restraints^e^**																			
			EHR audit	✓								✓		✓		✓		✓		✓	
		**Falls^e^**																			
			EHR audit	✓								✓		✓		✓		✓		✓	
		**Weight loss^e^**																			
			EHR audit	✓								✓		✓		✓		✓		✓	
		**Medication management^e^**																			
			EHR audit	✓								✓		✓		✓		✓		✓	
		**Behaviors of concern**																			
			EHR audit	✓								✓		✓		✓		✓		✓	
		**Choking**																			
			EHR audit	✓								✓		✓		✓		✓		✓	
		**Infection**																			
			EHR audit	✓								✓		✓		✓		✓		✓	
		**Unplanned hospital admission**																			
			EHR audit	✓								✓		✓		✓		✓		✓	
		**Wounds**																			
			EHR audit	✓								✓		✓		✓		✓		✓	
	**Business outcomes**																				
		**Cost of quality**																			
			Cost analysis	✓																✓	
		**Workforce productivity**																			
			Self-report survey	✓								✓		✓		✓		✓		✓	
	**End user**																				
		**User satisfaction**																			
			Self-report survey	✓								✓				✓				✓	
		**User experience**																			
			Self-report survey and interviews			✓		✓		✓										✓	

^a^DPU: defects per unit.

^b^EHR: electronic health record.

^c^DPO: defects per opportunity.

^d^DPMO: defects per million opportunities.

^e^National Quality Indicator Program (NQIP) outcome.

### Primary Outcome

The primary study outcome is data quality measured using DPU, DPO, DPMO and Sigma level. Improvement in data quality from T_0_ to 12 months after optimization will be determined by a reduction in DPU, DPO, and DPMO and an increase in Sigma level. A well-performing process should operate at a Sigma level of 6 and have ≤3.4 DPMO [43].

### Secondary Outcomes

#### Care Delivery

Care delivery will be measured by the proportion of weekly direct care time spent with residents using a self-report version of the Work Measurement Tool developed by Munyisia et al [52], which measures 8 categories of care activities in Australian RACFs, including *direct care, medication management, communication, documentation, indirect care, personal, in-transit*, and *other*. Clinical and care staff will be invited to complete self-report surveys from T_0_ to 12 months after optimization to provide a measure of workflow before and after optimization. Self-reported activities will be validated against observer-rated activities for a random staff subsample.

#### Clinical Outcomes

Under the National Quality Indicator Program, Australian aged care providers are required to undertake mandatory reporting of 5 National Quality Indicator Program indicators as a measure of the quality of clinical services and care provision [53]. These include *pressure injuries, physical restraints, falls, unplanned weight loss*, and *medication management*. In addition, Brightwater routinely measures 5 internal clinical indicators of quality across both aged care and disability services (behaviors of concern, choking, infection, unplanned hospital admission, wounds; Table 5). This study will measure changes in clinical outcomes from T_0_ to 12 months after optimization.

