### Study Phases

#### Overview

Figure 1 outlines DMAIC phases of the study. Stage 1 (*baseline*) will measure existing clinical data quality across services, identify root causes of data quality issues, and generate solutions to directly inform optimization. Stage 2 (*optimization*) will implement and test changes to clinical documentation processes and information systems specific to aged care and disability services. Stage 3 (*evaluation*) will measure the short-term (1-3 months) and long-term (4-12 months) changes in data quality and clinical and business outcomes following optimization.

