##### Phase 1.2: Measure

The measure phase will focus on measuring the baseline (T_0_) quality of clinical data across services and identifying key data quality issues. T_0_ data quality will be measured through an audit of client EHRs using a 6-month lookback period. Data quality will be measured in terms of the *number of defects* present in EHRs, measured using the CTQ metrics identified by the expert group.

Specifically, T_0_ data quality will be measured by the number of defects per unit (DPU), defects per opportunity (DPO), defects per million opportunities (DPMO), and the Sigma level (Table 4). T_0_ data quality will be measured for each of the 8 programs to allow the identification of any systematic variation between sites and service-specific data quality issues. In addition, the assessment will identify the most common types of defects across services to inform system optimization.

**Table 4 table4:** *Six Sigma* metrics for measuring defects.

Metric	Formula	Description
DPU^a^		Measures the average number of defects present in a unit (ie, the average number of defects in each client EHR^b^)
DPO^c^		Measures the number of defects as a proportion of the total number of data fields (ie, opportunities) present in each client EHR
DPMO^d^		Measures the number of DPO expressed per million
Sigma level	Determined from conversion tables using calculated DPMO	Measures the amount of variability in a process. *Six Sigma* quality performance is defined as 3.4 DPMO.

^a^DPU: defects per unit.

^b^EHR: electronic health record.

^c^DPO: defects per opportunity.

^d^DPMO: defects per million opportunities.

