### Quantitative Analysis

Quantitative analyses will be conducted using STATA (version 16.0; StataCorp LLC) [55]. Multilevel mixed effects regression models will be used to evaluate any change in primary and secondary outcomes from T_0_ to 12 months after optimization. For clustered longitudinal data, multilevel modeling recognizes that a change in outcome is affected by a fixed effect (ie, implemented changes) and random effects at both individual and group levels and can explicitly account for this multilevel random variation [56].

An a priori power calculation was performed to determine the minimum number of EHRs required to be evaluated to detect a significant change in our primary outcome (ie, data quality measured using DPU, DPO, DPMO, and Sigma level) from T_0_ to 12 months after optimization. First, we used G*Power [57] to compute the required sample size to detect a medium difference (*f*=0.15) at a Cronbach α level of .05 and a power level of .80 using a linear multiple regression analysis with *k*=3 fixed predictors (time, program, and the time × program interaction), which returned a required sample size of 77.

This was multiplied by the anticipated *design effect* [58], which is an adjustment factor for clustering in multilevel models. The design effect is calculated as:

1 + [(*n −* 1) × ICC]                       **(1)**

where n is the expected number of subjects per cluster and “ICC” is the intracluster coefficient or the expected correlation within clusters [58]. We defined a cluster as a facility (ie, site) with a median cluster size of 30 clients per facility. With an anticipated moderate intracluster coefficient of 0.10, the design effect is equal to 3.9, giving a required sample size of 77 × 3.9 = 300. On the basis of the occupancy rates and client population size (n=2200) as of January 2022, our primary outcome analysis will have sufficient statistical power.

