## Results

As of June 1, 2022, stage 1 commenced with T_0_ data quality audits conducted to identify the current data quality and system strengths and limitations. T_0_ data quality audits will be followed by user consultations to identify root causes of data quality issues. Clinical information requirements will be developed by May 2023 to inform optimization (stage 2) and evaluation (stage 3). Results are expected to be published in June 2023.

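### Clinical outcomes have a single T0 and no season-matched baseline, so the 1- to 9-month comparisons can mix season with the effect of optimization

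*Protocol article*

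**What the plan says.** Under Clinical Outcomes, the contrast is with T0: "This study will measure changes in clinical outcomes from T_0_ to 12 months after optimization". Stage 3: Evaluation sets the schedule: "Outcomes will be measured at T_0_ and at 1, 3, 6, 9, and 12 months after full optimization". Table 5 names EHR audit as the source for all ten clinical indicators, with one mark at T0, none in the sprint columns and one at each of the five follow-up points.

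The Overview of Study Phases commits Stage 3 to an early and a late reading; it "will measure the short-term (1-3 months) and long-term (4-12 months) changes in data quality and clinical and business outcomes following optimization".

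The only baseline window stated anywhere is in Phase 1.2: Measure, and it concerns data quality: T0 "data quality will be measured through an audit of client EHRs using a 6-month lookback period". No window is given for the clinical indicators, at T0 or at follow-up.

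Quantitative Analysis describes a multilevel model in which "a change in outcome is affected by a fixed effect (ie, implemented changes) and random effects at both individual and group levels". No concurrent control, repeated pre-optimization measurement or calendar matching is described.

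**The concern.** Five measurements spread over 12 months pass through every season. A single baseline value covering less than a full year cannot match all of them. Where an outcome has a seasonal cycle, part of the difference between an early follow-up point and T0 may then be season. Infection and unplanned hospital admission are the plausible candidates among the ten.

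This is separate from a long-term trend, and it sits in the measurement schedule. Calendar month and time since full optimization advance together, and the indicators have only one scheduled pre-optimization value. If the effect may differ at each follow-up time, a season term cannot be estimated from the scheduled data. It could be recovered only by assuming a shape for the effect.

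At stake is the short-term clinical reading. A seasonal rise could look like early harm or hide a benefit, and a seasonal fall could look like benefit. The Discussion anticipates a major impact on clinical outcomes and plans wide dissemination, so a false signal in either direction would matter. The primary outcome, data quality, is not affected by this point.

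**Working it through.** The plan states no figure on season, so there is none to reproduce. Its sample-size figures (77 and 300) concern the primary outcome and play no part here.

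**Calendar (inferred).** The Results section says: "As of June 1, 2022, stage 1 commenced with T_0_ data quality audits". A 6-month lookback from 1 June 2022 covers about December 2021 to May 2022. Inputs to Stage 2 are due by May 2023, and Stage 2 lasts 12 months, so full optimization falls about May to June 2024. Taking 1 June 2024, months 1 to 3 are June to August (southern winter), month 6 ends the spring, month 9 the summer and month 12 the autumn. The article gives no Stage 2 start date and expects results in June 2023. That fits these dates poorly unless it refers to Stage 1 alone.

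**Illustrative seasonal model (assumed).** Let t be calendar months with 1 January = 0. The rate relative to the yearly mean is 1 + A·cos(2π(t − 6.5)/12), which peaks in mid-July. There is no true effect of optimization. With w = 2π/12, the mean rate over a window from a to b is

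1 + A·[sin(w(b − 6.5)) − sin(w(a − 6.5))] / [w(b − a)].

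A = 10%, 20% and 30% correspond to peak-to-trough ratios of 1.1/0.9 = 1.22, 1.2/0.8 = 1.50 and 1.3/0.7 = 1.86.

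**Worked case, A = 20%.**
- T0, December to May (a = −1, b = 5): 1 + 0.2 × (−1.414/3.142) = 0.910.
- Month 1, June only (a = 5, b = 6): 1 + 0.2 × (0.448/0.524) = 1.171. Ratio 1.171/0.910 = 1.29.
- Month 1, 6-month lookback (a = 0, b = 6): 1 + 0.2 × (−0.518/3.142) = 0.967. Ratio 0.967/0.910 = 1.06.

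**Ratio to a 6-month T0 with no true effect:**

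| Follow-up window | A | 1 mo | 3 mo | 6 mo | 9 mo | 12 mo |
|---|---|---|---|---|---|---|
| Since previous point | 10% | 1.14 | 1.14 | 1.05 | 0.95 | 1.05 |
| Since previous point | 20% | 1.29 | 1.30 | 1.10 | 0.90 | 1.10 |
| Since previous point | 30% | 1.45 | 1.48 | 1.16 | 0.84 | 1.16 |
| 6-month lookback | 10% | 1.03 | 1.09 | 1.09 | 1.00 | 1.00 |
| 6-month lookback | 20% | 1.06 | 1.20 | 1.20 | 1.00 | 1.00 |
| 6-month lookback | 30% | 1.10 | 1.31 | 1.31 | 1.00 | 1.00 |

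The longer window softens the seasonal distortion at month 1, but 6 − 1 = 5 of its months precede full optimization, so it is not a clean short-term reading.

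**If the dates are left open.** Over all start months, a 1-month window against a 6-month T0 gives ratios of 0.85 to 1.17 (A = 10%), 0.71 to 1.37 (20%) and 0.59 to 1.60 (30%). The direction is therefore not fixed.

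**Matched baseline.** A follow-up window compared with the same calendar months of a pre-optimization year has a purely seasonal ratio of 1.00 by construction. A 12-month baseline against the 12-month post-optimization period also gives 1.00.

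**The case against.** The case against has several good parts.

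- The 6-month lookback is stated for data quality only. Applying it to the indicators is an inference from the shared EHR audit source, and an article may leave indicator windows to a fuller document. This stands: the article does not show that the clinical T0 covers half a year. Equally, it states no longer clinical baseline.
- The contrast named under Clinical Outcomes ends at 12 months, where season may nearly match T0. This stands on the inferred calendar, and it confines the point to the earlier readings. Those readings are nevertheless planned in the Overview.
- An unseen analysis plan could add a season term, and the three predictors listed under Quantitative Analysis belong to the primary-outcome power calculation. Both are true. A season term would still need pre-optimization data that Table 5 does not schedule, although longer indicator series may exist and nothing rules out using them.
- A seasonal mechanism is plausible for two of the ten indicators and is not argued for the rest. This stands.

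A reader might infer that seasonal swings will be reported as an early harm of 20% to 50%. The documents do not support this: they give no seasonal rates, the calendar is inferred, and with 6-month windows and A = 20% the distortion at months 1 and 3 is 6% and 20%.

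A reader might also infer that the plan expects a clinical learning curve of the same shape. It does not: the early increase described under Stage 3: Evaluation concerns time spent on documentation.

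**Conclusion.** The concern holds in a limited form. With one T0, no sprint measurements and no described control, the comparisons at 1, 3, 6 and 9 months can confound season with optimization for outcomes that vary by season, chiefly infection and unplanned hospital admission. The description of the model's fixed effect as the implemented changes leaves no room for this.

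The size cannot be fixed from the documents. On the inferred calendar, with the assumed mid-July peak and A = 20%, it is about 6% to 30% at months 1 and 3, depending on window length. Other dates could reverse the sign. The 12-month comparison ranges from no distortion (6-month windows) to about 10% (window since month 9) under the same assumptions. The point bears on secondary outcomes and their early interpretation, not on the primary analysis.

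**What to change.** State the window for each clinical indicator at T0 and at follow-up. For the routinely recorded indicators, where records allow, extract the 12 months before the first sprint by calendar month, or by the indicator's reporting period. Compare each follow-up period with the same calendar period of that year, using windows of equal length and rates per client-day. Base any short-term clinical claim on these matched comparisons.

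The data are likely to exist. The article says reporting of the five national indicators is mandatory for aged care providers, and that "Brightwater routinely measures 5 internal clinical indicators of quality across both aged care and disability services". The latter group includes infection and unplanned hospital admission.

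The cost is a longer retrospective extract and a change of wording. The article does not confirm that month-level records are retained for every indicator, hence the proviso. One prior year also leaves year-to-year variation in place, so matched differences should still be interpreted with caution.

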#### Business Outcomes

A cost of quality (CoQ) analysis [54] will be undertaken to compare the operational costs before and after optimization. The CoQ analysis is a critical part of the LSS framework to estimate the ongoing operational costs of optimizing the data or information system and to ensure that the expenses associated with achieving higher data quality are balanced against the costs of poor quality, which is defined as expenses incurred on resources and non–value-added activities to fix poor-quality data. CoQ costs include costs incurred on the optimization, ongoing operation, and maintenance of the data or information system, whereas poor-quality costs include costs incurred on activities such as data cleaning, data quality inspection, and meetings to rectify data inconsistencies. A health economist will be employed to undertake the CoQ analysis.

In addition, workforce productivity will be evaluated before and after optimization in relation to regulatory reporting. Corporate staff will be invited to complete self-report surveys from T_0_ to 12 months after optimization to provide an estimate of the number of hours worked to complete regulatory reporting activities before and after optimization.

#### User Satisfaction

Finally, self-report surveys and qualitative interviews will be used to measure changes in user satisfaction with clinical data systems before and after optimization. Prior research has shown that clinical documentation burden is a major driver of burnout among care staff [14,15] and can negatively impact job satisfaction [17]. Therefore, user satisfaction is an important outcome of this study.

### Quantitative Analysis

Quantitative analyses will be conducted using STATA (version 16.0; StataCorp LLC) [55]. Multilevel mixed effects regression models will be used to evaluate any change in primary and secondary outcomes from T_0_ to 12 months after optimization. For clustered longitudinal data, multilevel modeling recognizes that a change in outcome is affected by a fixed effect (ie, implemented changes) and random effects at both individual and group levels and can explicitly account for this multilevel random variation [56].

An a priori power calculation was performed to determine the minimum number of EHRs required to be evaluated to detect a significant change in our primary outcome (ie, data quality measured using DPU, DPO, DPMO, and Sigma level) from T_0_ to 12 months after optimization. First, we used G*Power [57] to compute the required sample size to detect a medium difference (*f*=0.15) at a Cronbach α level of .05 and a power level of .80 using a linear multiple regression analysis with *k*=3 fixed predictors (time, program, and the time × program interaction), which returned a required sample size of 77.

This was multiplied by the anticipated *design effect* [58], which is an adjustment factor for clustering in multilevel models. The design effect is calculated as:

1 + [(*n −* 1) × ICC]                       **(1)**

where n is the expected number of subjects per cluster and “ICC” is the intracluster coefficient or the expected correlation within clusters [58]. We defined a cluster as a facility (ie, site) with a median cluster size of 30 clients per facility. With an anticipated moderate intracluster coefficient of 0.10, the design effect is equal to 3.9, giving a required sample size of 77 × 3.9 = 300. On the basis of the occupancy rates and client population size (n=2200) as of January 2022, our primary outcome analysis will have sufficient statistical power.

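### The power statement gives the effect as f=0.15, but N=77 is obtained only with f²=0.15 (f=0.39), so the effect behind the 80% power and the 300-EHR minimum is misstated

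*Protocol article*

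**What the plan says.** The Quantitative Analysis section of the protocol article sets out one power calculation, for the primary outcome (data quality). G*Power was used to "compute the required sample size to detect a medium difference (*f*=0.15"), "at a Cronbach α level of .05 and a power level of .80", in a linear multiple regression with three fixed predictors: time, program and their interaction. The result is reported as "which returned a required sample size of 77".

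That figure is then inflated for clustering by site, taking "a median cluster size of 30 clients per facility". The text continues: "With an anticipated moderate intracluster coefficient of 0.10, the design effect is equal to 3.9", "giving a required sample size of 77 × 3.9 = 300". The section presents 300 as the smallest number of EHRs that must be assessed, and concludes that power is sufficient because the client population was 2,200 in January 2022.

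Table 3 shows how the records will be audited. Completeness, currentness and usability are taken from the data warehouse for every EHR. Accuracy and clarity are assessed manually on random samples whose size the article does not give.

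**The concern.** In regression power calculations the effect is entered as f², and f is its square root. The two scales are far apart here: f²=0.15 corresponds to f=0.39, while f=0.15 corresponds to f²=0.0225. The article prints f, yet the sample size it reports belongs to f².

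The stated 80% power is therefore attached to the wrong effect. As printed, a reader would take it that 300 EHRs suffice to detect an effect explaining about 2% of the variance. The calculation supports one explaining about 13%. The minimum of 300 inherits the mismatch because it is 77 multiplied by the design effect. It is also the only sample-size figure the article offers for the manually sampled metrics, so an audit held to that number would be read as more sensitive than it is.

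**Working it through.** **Inputs, all from Quantitative Analysis:** effect 0.15 (printed as f); alpha .05; power .80; k=3 predictors; N=77; cluster size 30; ICC 0.10; 2,200 clients.

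**Method.** Overall F test of a fixed-predictor regression, using the noncentral F distribution with df1 = 3, df2 = N − 4 and noncentrality λ = f² × N. Also R² = f²/(1 + f²).

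**1. Reproducing the article's figure.** Enter 0.15 as f²:
- f = √0.15 = 0.387; R² = 0.15/1.15 = 0.130.
- At N=77, λ = 0.15 × 77 = 11.55 and power = 0.802.
- The smallest N reaching 80% is 77, an exact match.
- Design effect: 1 + (30 − 1) × 0.10 = 3.9, and 77 × 3.9 = 300.3. Both match.

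**2. Taking the printed f=0.15 literally.**
- f² = 0.15² = 0.0225; R² = 0.0225/1.0225 = 0.022.
- At N=77, λ = 0.0225 × 77 = 1.73 and power = 0.164.
- The smallest N reaching 80% is 489, and 489 × 3.9 = 1,907.

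**3. Could another reading of the sentence give 77?**

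| Reading | N for 80% power |
|---|---|
| f²=0.15, 3 df tested | 77 |
| f²=0.15, 2 df tested | 68 |
| f²=0.15, 1 df tested | 55 |
| f²=0.15, one-sided test of one coefficient | 43 |
| 0.15 taken as R² | 66 |
| f=0.15, 3 df tested | 489 |
| f=0.15, 2 df tested | 432 |
| f=0.15, 1 df tested | 351 |
| f=0.15, one-sided test of one coefficient | 277 |

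Only the first row returns 77.

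**4. Power at a literal f=0.15 for different numbers of EHRs**, applying the article's design effect of 3.9 throughout:

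| EHRs | Effective N | Power |
|---|---|---|
| 300 (stated minimum) | 300/3.9 = 76.9 | 0.164 |
| 1,029 (site-based programs in Table 2: 750+31+101+53+23+71) | 263.8 | 0.507 |
| 2,200 (stated client population) | 564.1 | 0.859 |

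The 1,029 row is shown because a cluster is defined as a site, and Table 2 lists no sites for the two home-based programs.

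**The case against.** The best defence is that this is a printing slip. The number 77 is reproduced exactly at f²=0.15, so the intended quantity was very probably entered and the square lost in the text. With the label corrected, 77, 3.9, 300 and 80% all stand. That is accepted.

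A reader might infer that the study has 16% power instead of 80%. The document does not support this. The 16% needs two conditions together: that f=0.15 really was the target, and that no more than 300 EHRs are analysed. The article gives 300 as a floor, rests its adequacy claim on 2,200 clients, and audits every record for three of the six metrics. Even at f=0.15, about 1,907 is below 2,200, and power with all clients would be about 86%. The reassurance is partial, because the manual samples have no stated size and power is about 51% if only clients in site-based programs count.

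A reader might also convert f²=0.15 to a before-after difference of 2 × 0.387 = 0.77 SD and conclude that only large changes are detectable. That conversion assigns all the explained variance to a balanced contrast of independent groups at T0 and 12 months. The article spreads the effect over time, program and their interaction, and plans multilevel models for longitudinal data. The conclusion does not follow, and the word medium need not be removed on that ground.

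**Conclusion.** The concern holds as a misstatement of the effect size. The printed f=0.15 and the printed N=77 cannot both be right under the stated regression, alpha and power. The effect that matches the 80% power and the minimum of 300 EHRs is f²=0.15, explaining about 13% of variance and not 2.2%. If the printed value were the true target, the minimum would be more than six times too small (489/77 = 6.4).

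The likelier case is a missing square, which changes the stated effect and no other figure. This rests on the overall three-df F test, the only reading tried that returns 77, and on taking the article's design effect as given. It does not show that the study as planned is underpowered.

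**What to change.** In Quantitative Analysis, replace f=0.15 with f²=0.15 (f=0.39, R²=0.13). The figures 77, 300 and 80% then stay as they are and no further records are needed.

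If f=0.15 was truly the target, restate the required sample as 489 before and about 1,907 after the design effect, or keep 300 and give its power as 16%. The sponsor can settle which applies by checking the value entered in G*Power.

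In the same sentence, call .05 the significance level. Cronbach α is a reliability coefficient and has no place here; this is a wording slip that affects no number.

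The cost in the likely case is one edited sentence. In the other case it is a larger stated minimum, still within the 2,200 clients, or a lower stated power.
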